### Procedure for unblinding if needed {17b}

The design is open label with only outcome assessors being blinded so unblinding will not occur. Interim reports for the Data Monitoring Committee (DMC) and Trial Steering Committee (TSC) regarding recruitment, follow-up and baseline characteristics are unblinded. Interim safety reports (morbidity and side effects) for the DMC will be initially blinded but can be unblinded on request of the DMC if differences are observed.

## Data collection and management

### Plans for assessment and collection of outcomes {18a}

A chart outlining the surveillance system is provided in Fig. 6.

**Fig. 6 Fig6:**
[figure not shown]
Surveillance system process

In total, 103 incentivised FCHVs, with support from 8 interviewers, will monitor menstrual status in paper registers every 4 weeks. Interviewers collect data on all trial participants at enrolment (< 20 weeks) and at 30 ± 2 weeks’ gestation, covering primary, secondary and process outcomes. Six specialised dietary data interviewers undertake two 24-h dietary recalls at 30 ± 2 weeks’ gestation on non-consecutive days but within approximately 1 week of one another. They interview the woman and her husband/or a senior adult male household member if the husband lives away. If there are no adult males, the mother-in-law (or other female household head) is interviewed.

#### Electronic data collection

Questionnaires are programmed in Nepali, Awadhi and English on android operating system tablets or mobile phones using the CommCare electronic data collection platform [92]. In-built jump-sequences and value limits prevent entry of data outside plausible ranges.

To enable seamless merging of data by participant and efficient case management and follow-up, unique identifiers (IDs) encoded into Quick Response (QR) codes are printed onto stickers. These are allocated to women enrolled by attaching them next to their names in menstrual monitoring registers. When a woman is enrolled in the trial, her QR code is attached to her a trial participant card (TPC) and to a trial participant list held by each interviewer. Her ID is scanned at every interaction with interviewers, dietary interviewers and NAs, enabling information stored in CommCare about that woman (such as name, LMP, and other details) to be ‘called up’ and used to ensure questionnaire flow and accuracy.

#### Standard operating procedures

To standardise haemoglobin concentration (Hb) measurements, anthropometric and 24-h dietary recall measurements, standard operating procedures (SOPs) are followed to ensure that measurements are accurate and inter-observer difference minimised. Hb is determined using a portable battery-operated electronic Haemoglobin Photometer (Hemocue Hb 301+, Angelhom, Sweden). The haemoglobin measurement follows standard procedures as per the manufacturer’s instructions. Anthropometric measures are taken following the WHO guidelines [93–95]. Mid-upper arm circumference (MUAC) and weight of women and their husbands are measured using Seca head circumference tapes (93/42/EEC) to the nearest millimetre, and Seca 877 weighing scales accurate to 100 g respectively. Heights are measured using portable Leicester Stadiometers. Calibration of Hemocue and scales are checked at least once per week by the interviewers. Videos on how to take anthropometric and Hemocue measurements have been developed for use during training and are installed on their tablets for reference. Interviewers’ tablets will be programmed to provide reminders for calibration checks and COVID-19 symptom checks as required. In the case of anthropometric measures, a third reading is required if the first two measures differ by more than a specified margin. Dietary intake assessments will follow standard protocols [96], including a five-stage multi-pass probing method to minimise underreporting [97].

#### Enrolment of trial participants

FCHVs are responsible for detecting pregnancies in their cluster as early as possible. Initially, the FCHVs and interviewers visit every identified woman to take her written consent for ongoing menstrual monitoring and to update information from the census (adding new women and households as appropriate). After consent has been taken in all clusters, trial enrolment starts. FCHVs record each consenting women’s LMP in the page of the register corresponding to her unique ID. The FCHVs subsequently visit every 4 weeks to record women’s menstrual/pregnancy status over a period of 7 months.

Once an FCHV finds a woman who has missed at least one period, she conducts a urine pregnancy test (UPT) at the woman’s house. If the UPT is positive, the interviewer visits the woman to check her eligibility and take her written consent to enrol in the trial. The interviewer provides each consenting eligible woman with a TPC with her unique QR code identification number affixed. If a woman is ineligible (≥ 20 weeks’ gestation, not planning to reside in the cluster, or unable to respond to questions), she is advised to seek ANC and, in the intervention arm only, is invited to join PLA women’s groups. In intervention clusters, interviewers notify the NAs about the location and gestational age of the newly enrolled eligible women to receive her first home visit and invite her to PLA groups.

When the interviewer takes informed written consent from women, they ask 5–6 questions to check the PW’s understanding of the trial process. Only those who can demonstrate that they have understood are enrolled. At both enrolment and primary outcome interactions, interviewers will measure the woman’s haemoglobin concentrations, height, weight and mid-upper arm circumference. We will also collect the woman’s age, parity, medical history, date of the last menstrual period, pregnancy symptoms/ problems, pregnancy intention as measured by the London Measure of Unwanted Pregnancy (LMUP), smoking and alcohol consumption, age of husband, household size and other socioeconomic and demographic information including caste/religion, education, landholdings and assets, and housing characteristics.

#### Outcome measurement in the third trimester of pregnancy

As listed in Table 1, all primary, secondary and process outcomes are measured at 30 ± 2 weeks. Although ideally during the 28-to-32-week window, due to potential disruption that the ongoing COVID-19 pandemic may cause, an outcome may be collected any time up to delivery as gestational age at measurement will be adjusted for in all analyses.

Dietary interviewers use an adapted quantitative 24-h dietary recall tool [98] to measure dietary intakes of PW and their husbands or another ‘senior’ male (or a female household head if there are no men). Recalls are taken twice on non-consecutive days after between 28 and 32 weeks, including typical and atypical (celebratory and fasting) days. Daily nutritional intakes are calculated using (i) a list of locally available foods; (ii) quantified intakes of each food, estimated using a combination of weighed methods (using food models) and a photographic atlas of graduated portion sizes [99] and (iii) a Food Composition Table that integrates nutritional composition data from Nepal [100–102], India [103], Bangladesh [104], USA [105], UK [106, 107] and published back-of-pack information from local foods [102].

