#### IFA supplementation and antenatal care

A Cochrane review of 44 randomised controlled trials found that iron supplementation during pregnancy reduced the risk of maternal anaemia at term by 70% [43]. Accordingly, IFA supplementation in pregnancy has been implemented in many LMICs, including Nepal since 1997. IFA is an integral part of the Government of Nepal (GoN)’s Safe Motherhood programme which also recommends at least four antenatal care (ANC) visits at health facilities at 4, 6, 8 and 9 months of gestation, though recently four additional antenatal ‘contacts’ with a skilled provider are also being recommended. PW are eligible to receive free IFA from 14 weeks gestation for 180 days of pregnancy and 45 days post-partum from health workers or female community health volunteers (FCHVs). If a PW is anaemic (< 11.0 g/dL), GoN recommends the daily IFA dose is doubled from 60 to 120 mg/day (per current WHO guidance [44]), though this is not routinely practised. All PW are also advised to take a single dose of 400 mg of albendazole after the first trimester to reduce the risk of anaemia from hookworm infection [45].

In 2016, Nepal was able to provide some IFA supplementation to 91% of PW, but only 42% completed the minimum 180-day IFA dose. Increasing adherence to IFA could reduce anaemia; a study from the *Terai* found higher odds of anaemia amongst women who took lower doses of IFA (≤ 143 vs ≥ 144 tablets) [46]. To maximise IFA intake, ANC needs to begin earlier in pregnancy [47]. In 2016, 31% of PW in Nepal had fewer than 4 ANC visits and 42% of rural women had their first ANC after 4 months [22]. In peri-urban breastfeeding Nepalese woman, anaemia appears to have been prevented through IFA supplementation. Women’s dietary iron adequacy was 30% and bioavailability of non-haem iron was low due to high levels of phytates in the diet, yet only 5% reported low plasma ferritin iron deficiency anaemia, suggesting that IFA had filled the gap [33]. In many places however, supply-side issues may still prevent women from receiving the necessary dose free of cost and some may discontinue IFA consumption due to side effects [47, 48].

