## Statistical methods

### Statistical methods for primary and secondary outcomes {20a}

A detailed Statistical Analysis Plan, drawn up by the trial statistician (AC) and Nepal principal investigator (NS), will detail the analysis strategies, covariate adjustment and the approach to any missing data. Each version is presented to the Data Monitoring Committee (DMC) and Trial Steering Committee (TSC) for approval and the first version is prepared before the first patient is recruited.

Primary analysis is by intention-to-treat and will use the standard 5% significance level. Analysis of the primary outcome (haemoglobin concentration at the 30 ± 2 weeks) is based on linear regression, with random effects to adjust for clustering. Analyses are conducted with and without adjustment for predictors of the primary outcome (Table 4) including socioeconomic status, parity, age of PW, gestational age at measurement, maternal education and characteristics used in the restricted randomisation (individual level religion, ethnicity and travel time to the nearest health facility and cluster-level number of eligible women from the pre-trial census).

**Table 4 Tab4:** Variables to adjust for or to use in subgroup analyses and exposure variables

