**Confounders/covariates to adjust for in analyses:**	
Wealth score constructed out of household assets	
Education status of pregnant woman (none, primary, secondary, higher secondary +)	
Parity (*n*)	
Age of pregnant woman in years	
Gestational age at measurement in weeks	
Baseline (study enrolment) measure of Hb (for primary outcome analysis)	

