**Main exposure (independent) variable for analyses of outcomes above:**	
Study arm: Home visiting +PLA versus Control (which is the reference group)	
**Within the intervention arm the levels of exposure to PLA women’s groups and home visits are coded in three (independent) variables for analyses of a dose-response effect upon the outcomes above (or a subset of them):**	
Exposure to women’s group—score of exposure constructed out of number of meetings attended by pregnant woman and number attended by family members	
Exposure to home visiting with tailored counselling and dose of iron-folic acid supplements—score of exposure constructed out of number of meetings attended by pregnant woman and number attended by family members	
IFA consumption during pregnancy (count or ordinal score constructed from the count)	

Our primary analysis will also adjust for haemoglobin at enrolment, to gain precision, but we acknowledge the trade-off that this may dilute intervention effects since in principle cluster-level intervention effects could be mediated through haemoglobin at enrolment. In a sensitivity analysis, we will remove adjustment for haemoglobin at enrolment.

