Analysis of secondary and impact pathway outcomes (Table 1) and of process indicators (reported in 1 or more separate publications (Table 2)) will follow a similar methodology. We will use linear regression for continuous outcomes, logistic regression for binary outcomes, ordinal logistic regression for ordinal outcomes and negative binomial regression for ‘count’ outcomes such as number of IFA consumed. For continuous and count outcomes, before analysis of intervention effectiveness, the distribution will be examined and in the event of skewed or heaped data transformations such as log will be considered, or methods will be adapted such as for zero-inflation. For energy, iron and other micronutrients, which are (almost) ubiquitously consumed, we will use our duplicate measure to account for the wide intra-individual variability with a nonlinear random effects model and person-specific random effects (the National Cancer Institute method). For intakes of recommended foods that are only episodically consumed but also have wide within-person variance, we use a two-part model where the probability of consumption is estimated using a multilevel logistic regression, the amount consumed on consumption days is estimated by fitting a multilevel nonlinear regression model and the error terms of the two parts are correlated [108].

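### Late outcome measurement is allowed because gestational age is said to be adjusted for in every analysis, but the statistical methods also plan analyses without it; the ANC and IFA counts are most exposed

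*Protocol article*

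**What the plan says.** The section on outcome measurement in the third trimester fixes one time point: "all primary, secondary and process outcomes are measured at 30 ± 2 weeks". It then widens the window as a pandemic contingency: "an outcome may be collected any time up to delivery as gestational age at measurement will be adjusted for in all analyses". Adjustment is the only reason given for accepting late measurements.

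The section on statistical methods for primary and secondary outcomes {20a} states: "Analyses are conducted with and without adjustment for predictors of the primary outcome (Table 4". The list that follows names the variable concerned: "predictors of the primary outcome (Table 4) including socioeconomic status, parity, age of PW, gestational age at measurement". In Table 4, "Gestational age at measurement in weeks" stands with the ordinary covariates and not under the adjustments for study design.

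For haemoglobin, the same section adds: "Our primary analysis will also adjust for haemoglobin at enrolment, to gain precision". Its sensitivity analysis removes enrolment haemoglobin only. Analysis of the secondary and pathway outcomes "will follow a similar methodology", with negative binomial regression for counts.

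Table 1 contains two running totals, each compared as a ratio of means: ANC visits at a health facility, and IFA tablets taken up to the date of measurement.

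**The concern.** The wider window rests on a promise that the analysis section does not keep. Read literally, the two sections cannot both be true. The analysis section is the one that will be followed when models are fitted, so some planned models will have no protection against differences in timing.

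This matters most for the two counts. For haemoglobin, a late reading is the same quantity at a later point in pregnancy. For ANC visits and IFA tablets, a late reading covers a longer counting period. If women in one arm tended to be measured later, the unadjusted ratio would mix an effect of the intervention with an effect of the calendar. The protocol also does not say whether the adjusted or the unadjusted model is the main one for the counts, which leaves the choice open until the data are in.

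**Working it through.** **Passages side by side**

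1. Outcome measurement section: gestational age at measurement is in all analyses.
2. Statistical methods {20a}: analyses are run both with and without a set that includes it.
3. Same section, on the primary model: enrolment haemoglobin is adjusted for in addition to the other covariates, so this model contains gestational age.
4. Same section, on secondary and pathway outcomes: a similar method, so models without gestational age are planned there too.

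Statements 1 and 2 conflict. Statement 3 limits the consequence for the primary result. Statement 4 extends it to the counts.

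**The plan's own power figure, to obtain a standard error**

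Inputs from the sample size section: 27 clusters per arm, 15.6 outcomes per cluster, SD 1.2, ICC 0.09, CV of cluster size 0.27, difference 0.4 g/dL, two-sided 5%.

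- Design effect = 1 + ((0.27² + 1) × 15.6 − 1) × 0.09 = 2.416
- Effective n per arm = 27 × 15.6 / 2.416 = 174.3
- SE of the arm difference = 1.2 × √(2 / 174.3) = 0.13 g/dL
- Power by normal approximation = 87.5%, against 88.3% in Table 3. This is close enough, and the power figure is not in dispute.

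**Growth of the counts with time**

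Assumption: one tablet a day with full adherence. The protocol gives two starting points for IFA, 14 weeks in the background section and 20 weeks in the adherence section. These need to be reconciled; both are used here only to show a range.

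| Start | By week 30 | By week 40 | Ratio |
|---|---|---|---|
| 14 weeks | 16 × 7 = 112 | 26 × 7 = 182 | 1.62 |
| 20 weeks | 10 × 7 = 70 | 20 × 7 = 140 | 2.0 |

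For ANC, the background section describes "at least four antenatal care (ANC) visits at health facilities at 4, 6, 8 and 9 months of gestation". At 52/12 = 4.33 weeks a month, week 30 is month 6.9 and week 32 is month 7.4. About two of the four visits are therefore due in the window, and all four by term.

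These figures compare one woman measured early with one measured late. They are not a bias between arms.

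**Bias between arms in an unadjusted IFA ratio**

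Assume no true effect. One arm has an excess share d of women measured at week L, and all others in both arms are measured at week 30. With start week s:

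ratio = 1 + d × (L − 30) / (30 − s)

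- Low: d = 0.10, L = 36, s = 14 gives 1 + 0.10 × 6/16 = 1.04
- High: d = 0.30, L = 40, s = 20 gives 1 + 0.30 × 10/10 = 1.30
- With d = 0 the ratio is 1.00, however large the excess for an individual woman.

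**Bias in unadjusted haemoglobin**

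Assumptions, none of them in the protocol: a change of 0.03 to 0.06 g/dL per week after 32 weeks, a mean delay of 5 weeks, and an arm difference of 10 to 20 percentage points in late visits.

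- Low: 0.10 × 5 × 0.03 = 0.015 g/dL, or 4% of 0.4
- High: 0.20 × 5 × 0.06 = 0.06 g/dL, or 15% of 0.4, and 0.06 / 0.13 = 0.46 of an SE
- Wider slopes of 0.02 to 0.10 g/dL per week with a 1-week difference in mean gestational age give 0.02 to 0.10 g/dL (5% to 25% of 0.4), at most 0.10 / 0.13 = 0.77 of an SE.

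**The case against.** The strongest reply is that the result that counts is already protected and that the details belong to an analysis plan that is not shown. Much of this stands, and it rules out several stronger readings that a reader might infer.

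- **That the primary result is unprotected.** It is not. The primary haemoglobin model is an adjusted one, and its sensitivity analysis drops only enrolment haemoglobin.
- **That gestational age enters as a single linear term.** Table 4 gives a variable and its unit, not a functional form. The form is properly left to the analysis plan.
- **That late measurement inflates the count ratios by itself.** Lateness shared by both arms raises both counts. The ratio is biased only if timing differs by arm and the model does not account for it. Gestational age as a covariate in a log-link count model already deals with much of the longer counting period.
- **That timing will differ by arm.** Interviewers make the outcome visits to target dates based on the last menstrual period, with no distinction by arm. The intervention home visits end by 26 weeks, and the stated cause of lateness, COVID-19, is not specific to an arm. On the other side, interviewers know the arm, and the women's groups continue in the intervention arm only. A difference is possible, not shown.
- **That the trial no longer answers its question.** The 28-to-32-week window remains the target, and the extension is a contingency. The dietary recalls are separately placed at 28 to 32 weeks, so the extension may not reach the dietary outcomes.

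What the reply does not remove is the conflict itself. Both statements are in the protocol, and no analysis plan can make both true.

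**Conclusion.** The point holds in a limited form. The only stated justification for measuring outcomes up to delivery is untrue for part of the planned analysis. The primary haemoglobin test is not affected. The exposed results are the analyses without gestational age, chiefly total ANC visits and IFA tablets.

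The possible size for IFA, a ratio of about 1.04 to 1.30 with no true effect, rests on assumed arm differences in late measurement, full adherence and one tablet a day. It falls to nothing if timing is balanced. The haemoglobin shift of 0.015 to 0.06 g/dL also rests on assumed slopes and delays, is under half a standard error, and concerns the unadjusted model only. No comparable between-arm figure was worked out for ANC visits.

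This should be fixed before outcome data are seen, but it does not threaten the trial's main conclusion.

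**What to change.** 1. Reconcile the outcome measurement section with the statistical methods section by keeping gestational age at measurement in every model, including the minimally adjusted one.
2. Name the model with gestational age as the main analysis for ANC visits and IFA tablets. Alternatively, count both only up to a fixed gestational age, where recorded dates allow it.
3. Report gestational age at measurement by arm.
4. Pre-specify a sensitivity analysis limited to women measured at 28 to 32 weeks. It selects on something that happens after randomisation, so it checks the main analysis and does not replace it.

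A spline for gestational age or a log offset in the count models could be considered but is not required. An offset forces counts to be proportional to time, which scheduled ANC visits are not.

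The cost is a change of wording and one extra analysis with somewhat fewer women. Items 1, 3 and 4 need no new data. The protocol states that recruitment had not begun at this version, so the change could be made before any outcome was collected.

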#### Monitoring and supervision of data collection

All interviewers are supervised by field coordinators and a monitoring manager who observe 5% of interviews, take replicate measures of anthropometry and monitor electronic form submissions. The monitoring team meets monthly and Kathmandu-based team members visit and/or hold video-conferencing meetings periodically to provide support. Problems with electronic forms are logged and corrections made reversibly in the data using Stata data cleaning ‘do’ files. A Kathmandu-based data management team monitors data daily.

### Plans to promote participant retention and complete follow-up {18b}

Strategies to promote participant retention include collecting and updating phone numbers of respondents so interviewers can arrange a convenient time to visit; and providing a small gift at the end of data collection. Within the CommCare forms, target dates for intervention and follow-up events, based on the LMP, are displayed on customised lists by user to help interviewers follow the schedule.

